**9.11.**

**Subgroup analyses**

*A priori* we identified the following subgroups for subgroup analyses: age ≤5 vs ≥6 years,53,70 sex,71 post-randomization PRAM score, personal atopy, non-rhinovirus viral nasal pathogen, and “acute viral induced wheeze” phenotype (age ≤5 years without atopy or cough between respiratory infections).72,73 For subgroup analyses, we will use generalized linear mixed modelling with treatment group-subgroup interaction factor, controlling for site and age randomization factors. *Sex subgroup analysis* **–** while we are unable to stratify randomization by sex due to feasibility, sex will be considered in a pre-identified key subgroup analysis.

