**OBJECTIVES AND END POINTS**

**Primary question:** In children 2.00-17.99 years old who present to 6 PERC EDs with acute asthma and have persistent moderate-severe asthma after initial optimal standardized therapy, is there a greater reduction (improvement) in the PRAM score at 120 minutes post- intervention start in those given IVMg (75 mg/kg, max 2.5 g), compared to placebo?

**Primary endpoint:** PRAM score at 120 minutes post start of experimental therapy.

**Secondary questions:** Between these treatment modalities:

a)

b)

Is there a difference in the hospitalization rate for asthma at the index ED visit?

Is there a difference in the hourly changes in the PRAM, respiratory rate, heart rate oxygen saturation and blood pressure from the pre-intervention baseline to 180 minutes?

Is there a difference in the area under the receiver operating characteristic curve for PRAM within 120 minutes?

Is there a difference in the proportion of children achieving PRAM indicating mild asthma status, i.e. ≤ 3 points (widely accepted criterion for discharge home) at 120 minutes?

Does the treatment effect on the primary outcome vary between subgroups defined by: age, sex, pre-randomization PRAM, atopy, non-rhinovirus nasal pathogen36 and “viral-wheeze” phenotype?

Is there a difference in the hospitalization rate for asthma within 72 hours of ED discharge?

Is there a difference in the rate of unscheduled visits for asthma within 72 hours of ED discharge?

Is there a difference in the overall hospital length of hospital stay? Is IVMg a cost-effective treatment option?

c)

d)

e)

f)

g)

h)

i)

**Secondary endpoints:** PRAM, oxygen saturation, heart rate and resp rate 30, 60, 120, 180 minutes and blood pressure 10, 20, 30, 60, 120, 180 minutes after start of experimental therapy and unscheduled medical re-visits/hospitalizations for asthma 72 hours after ED discharge home.

Version Date: June 25, 2025 (v3.0)

Page **14** of **54**

[figure not shown]

**MAGICIAN** Clinical Trial Protocol

**Hypothesis:** Based on a two-tailed hypothesis, children with PRAM ≥ 5 after initial therapy given IV Mg will have a mean PRAM improvement at 120 minutes post IVMg ≥1.0 point greater compared to placebo.

**4.**

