**6.5. Measures to Minimize Bias: Randomization and Blinding**

**Treatment allocation:** The leading site pharmacy will use the randomize.net tool to produce the study Master Randomization tables, stratified by site and age group (< 6years old, i.e. prior to 6th birthday vs ≥6 years old as pre-schoolers may respond differently to asthma therapies),52 employing permuted randomization of varying block sizes in a 1:1 ratio of Mg sulfate to placebo. The study nurse will transcribe the assigned study kit numbers into the secure Health Canada-validated REDCap database.

Master lists will be provided to all participating research pharmacies which will permit the preparation of the study kits according to the randomization schedule.

Version Date: June 25, 2025 (v3.0)

Page **20** of **54**

[figure not shown]

**MAGICIAN** Clinical Trial Protocol

The patients, outcome assessors (study nurses, ED physicians) and investigators will be blinded to treatment assignment; the pharmacy will be unblinded. The SickKids research pharmacist will provide a manual with instructions on how each pharmacy will prepare blinded numbered kits with Mg or 0.9% saline placebo, according to routine IVMg sulfate infusion protocols (**Section 6.4.3 Logistics of Blinding and Kit Making)**. Each site will receive requirements for drug accountability and handling. Unblinding is unlikely and did not occur in MAGNUM. The active Mg and saline placebo are identical in volume, color, odor, and appearance. Further, children with unstable airway will be excluded and only 6% experience a mean BP drop 5mmHg after IVMg with fewer requiring intervention.10

Administration of open-label IV-Mg would highly increase the probability of study contamination and will be strongly discouraged until after 120 minutes after the start of the experimental therapy. Children not responding to/worsening after the experimental therapy will be given back-to-back administration of inhaled salbutamol, other required medications and supplemental oxygen if necessary. In the highly exceptional event of impending respiratory failure after the intervention (children with unstable airway on arrival will be excluded), immediate open-label IVMg will be permitted with locally used Mg doses, but unblinding will not be needed because a 2nd Mg infusion is safe for normotensive patients.47-49,51,60 (**Section**

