**STATISTICAL CONSIDERATIONS**

**9.1. Sample size**

Sample size is based on the assessment of the PRAM change in the IVMg vs the control group and we *conservatively* aim for an inter-group PRAM difference in change of ≥1.0 point (SD 2.5), based on the following evidence. Children 1-17 years old with a baseline PRAM ≥4 points had a median PRAM change of 3 points if discharged vs.1 point if admitted.25 In a PRAM validation study of children with moderate dyspnea anchored against expert physician-perceived clinical improvement a PRAM change of 1.5 (SD 2.3) was seen for children judged clinically improved vs. 0.0 (SD 2.2) for those unchanged.67 When compared to a change in respiratory rate percentile, a PRAM change of 1.1 (SD 2.7) was seen in the improved patients vs.0.3 (SD 2.2) in those unimproved.67 Based on this evidence, the investigators agree that a minimally clinically significant difference in PRAM changes between groups is 1 point. Although the study non- compliance and loss to follow-up rates in MAGNUM were both 0%, we conservatively assume that the non-compliance (crossover) with allocated therapy and the follow up loss may be as high as 5% and 1%, respectively. Based on these parameters, a study sample of 192 children (96 per group) provides 80% power with a two-sided significance level 0.05. Accounting for the randomization factors of site and age, a sample of 192 children obtained by recruiting in 12 strata (2 ages x 6 sites) with a similar number of children per strata, a significance level of 0.05 and an intracluster correlation coefficient of 0.05, achieves 80% power to detect PRAM difference in change of 1.0 (SD 2.3) based on a mixed-model analysis.

Version Date: June 25, 2025 (v3.0)

Page **24** of **54**

[figure not shown]

**MAGICIAN** Clinical Trial Protocol

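### The viral-wheeze subgroup exists only at age ≤5, so the interaction model stated in Protocol 9.11 cannot separate a phenotype effect from an age effect on the response to magnesium

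*Protocol*

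**What the plan says.** Section 3 of the protocol asks, as secondary question (e), "Does the treatment effect on the primary outcome vary between subgroups defined by: age, sex, pre-randomization PRAM, atopy" and further factors, the last of which is the viral-wheeze phenotype. Age and phenotype are thus listed as separate possible modifiers.

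Section 9.11 sets the age cut at "age ≤5 vs ≥6 years" and describes the viral-wheeze subgroup as a "phenotype (age ≤5 years without atopy or cough between respiratory infections". Both use the same age boundary. For all subgroups it prescribes "generalized linear mixed modelling with treatment group-subgroup interaction factor, controlling for site and age randomization factors". It does not restrict the phenotype analysis to preschoolers, and it mentions no treatment-by-age term alongside the phenotype interaction.

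Section 6.5 stratifies randomization by age (before the 6th birthday versus older) and gives the reason: "as pre-schoolers may respond differently to asthma therapies". The protocol itself therefore allows that age may modify the treatment effect.

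**The concern.** The phenotype is nested in the younger age group. Its complement is made up of preschoolers with atopy or interval cough together with every child aged 6 or older. Controlling for age as a randomization factor adjusts the level of the PRAM change in each age group. It does not let the treatment effect differ by age. The single interaction term therefore contrasts the effect in non-atopic preschoolers with the average effect in everyone else. That contrast is non-zero whenever the effect differs by age, even if phenotype makes no difference among children of the same age.

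At stake is the interpretation of one part of question (e). An age difference could be reported in part as a viral-wheeze difference. Conversely, a real phenotype difference among preschoolers could be diluted by the school-aged children.

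**Working it through.** **The plan's own figure.** The protocol gives no power for the phenotype interaction. For the primary outcome, section 9.1 says "a study sample of 192 children (96 per group) provides 80% power with a two-sided significance level 0.05", for a difference of 1.0 with SD 2.5. With 96 per group this reproduces as 79.1% (normal approximation) before any allowance for crossover or loss. N and SD are taken from there.

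**Inputs**
- N = 192, SD = 2.5, 1:1 allocation (sections 9.1 and 6.5).
- p, the share aged ≤5: 0.6. Section 9.2 gives 60% as the preschool share of asthma visits to pediatric EDs. Its use for the trial population is an assumption, varied over 0.5-0.7.
- q, the share of preschoolers with the phenotype: not in the document. 0.5 is assumed and varied over 0.2-0.6.
- D, the difference in magnesium effect between age groups: not in the document. Values of 0.5 to 2.0 are used.

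**Transfer of an age effect.** Suppose phenotype has no effect given age. The phenotype group consists wholly of preschoolers. School-aged children make up (1−p)/(1−pq) of the comparison group. With treatment balanced within age groups, the expected phenotype interaction is

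D × (1−p)/(1−pq) = D × 0.4/(1−0.3) = 0.57 D at p = 0.6, q = 0.5.

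**Standard error, stated model.** 2·SD·√(1/n₁ + 1/n₀), with n₁ = 192 × 0.6 × 0.5 = 57.6 and n₀ = 134.4: 5 × √(1/57.6 + 1/134.4) = 0.79.

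**Rejection at nominal 5%, by normal approximation**
- D = 0.5: 0.29/0.79, about 6.5%
- D = 1.0: 0.57/0.79, about 11%
- D = 1.5: 0.86/0.79, about 19%
- D = 2.0: 1.14/0.79, about 31%

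Simulation at the same setting gave 11.0%, 18.4% and 30.0% for D = 1.0, 1.5 and 2.0. With the treatment-by-age term added, the rates were 5.3%, 4.5% and 4.7%.

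**Sensitivity to q at p = 0.6** (rejection rates from simulation; N and SD as above)

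| q | Share transferred | SE, stated model | Rejection, D = 1 | Rejection, D = 2 | SE, preschoolers only |
|---|---|---|---|---|---|
| 0.2 | 0.455 | 1.11 | 6.6% | 10.7% | 1.16 |
| 0.4 | 0.526 | 0.84 | 9.7% | 21.8% | 0.95 |
| 0.5 | 0.571 | 0.79 | 11.0% | 30.0% | 0.93 |
| 0.6 | 0.625 | 0.75 | 13.0% | 38.2% | 0.95 |

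Over p = 0.5-0.7 and q = 0.2-0.6 the transferred share runs from 0.35 to 0.71. At q = 0.2, 0.4 and 0.6, the treatment-by-age term brings the mean spurious interaction to between −0.03 and 0.03 and the rejection rate to 4.5-5.5%.

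**Price in precision.** The ratio of the two standard errors is √[(1−pq)/(1−q)]. At p = 0.6 this is √(0.76/0.6) = 1.13 for q = 0.4 and √(0.7/0.5) = 1.18 for q = 0.5. It is 1.05 at q = 0.2 and 1.26 at q = 0.6.

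**Power for a true 2-point phenotype difference among preschoolers** (p = 0.6, q = 0.5, simulation). If school-aged children respond like the phenotype group, power is 19% as stated and 56% with the added term. If they respond like the other preschoolers, it is 70% and 57%.

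**The case against.** Four points can be made for the plan.

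First, section 9.11 names neither the reference group nor the full list of terms. The comparison with all other children, with age only as a main effect, is the plain reading and not verbatim. A statistical analysis plan not available here could specify otherwise. This stands as a caveat. The protocol does state a model, however, and that model as written does not separate the two factors.

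Second, age is part of the phenotype's definition, so the stated contrast answers a legitimate if cruder question: do these children respond differently from the rest of those enrolled? This stands. A reader might infer that question (e) is answered wrongly, but the document does not support that. The rejection rates above are false positives only for a phenotype effect at a given age.

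Third, age and personal atopy have their own prespecified interaction tests, so a large age effect would be seen alongside. That makes misreading less likely but does not correct the phenotype estimate. A reader might also infer that the phenotype result largely repeats the age result, or that an age effect passes into it whole. Neither holds: the transfer is partial, about 45-63% at p = 0.6.

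Fourth, the marked error rates need an age difference at least as large as the 1-point effect the trial is designed to detect, and the protocol gives no estimate of one. The gain is also limited. For a true 1-point phenotype difference, with school-aged children responding like other preschoolers, power is 22% as stated and 18% after the change (p = 0.6, q = 0.4). Both points stand and limit the weight of the concern.

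**Conclusion.** The concern holds as a matter of interpretation. On the plain reading of section 9.11, the viral-wheeze interaction mixes phenotype with age and cannot tell them apart. Roughly half of any age difference in the magnesium effect appears in it: 0.57 at 60% preschoolers and a 50% phenotype share. The false-positive rate for a phenotype effect given age is then about 11% for a 1-point age difference and about 30% for 2 points. At 0.5 points it is about 6.5%, near nominal.

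These sizes rest on SD 2.5, on applying the preschool share of ED visits to the trial, and on an assumed phenotype share. The affected analysis is one low-powered subgroup test among secondary analyses that section 9.7 calls exploratory. The primary analysis and the sample size are not touched.

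**What to change.** In section 9.11, add one sentence for the phenotype analysis only: the model also includes the treatment-by-age-group interaction, or it is fitted only in children before their 6th birthday. The treatment-by-phenotype term then compares preschoolers with and without the phenotype. Leave the age subgroup analysis unchanged.

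No new data are needed. The cost is that the contrast rests on preschoolers alone, about 115 of 192 (0.6 × 192). The standard error is about 13-18% larger at phenotype shares of 40-50%, and power is lower where school-aged children respond like the other preschoolers. If the wider contrast is also wanted, name its comparison group and interpret it next to the age interaction.

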**9.12.**

**Economic analysis**

We will assess the cost-effectiveness of IVMg to alleviate respiratory distress. We will use cost-utility analysis (CUA) to assess the incremental cost-effectiveness of IVMg vs placebo in terms of cost per quality-adjusted life year and cost-effectiveness analysis to assess cost per alleviating respiratory distress (PRAM ≤3). Using a decision tree, analyses will be undertaken from the perspective of the Canadian healthcare system over a 72-hour horizon which will conform to Canadian guidelines for economic evaluation.74

Comparative effectiveness of IVMg versus placebo will be derived from the MAGICIAN data, including PRAM ≤3 points at 3 hours (secondary outcome c); patient disposition (i.e., discharge or hospitalization during the index ED visit; secondary outcome a), resource use (secondary outcomes d–f), and adverse events. Costs will include drug acquisition and administration, healthcare resource use, and adverse event management. For the CUA, utilities will be sourced from the literature. Scenario analyses will include adopting a societal perspective. Further information can be found in Appendix E: Economic Analysis.

**9.13.**

**Adherence**

This is unlikely to be a problem since intervention delivery will be given in the ED. The experimental period is short and IV administration guarantees medication delivery.

Conservatively, we assume a 5% crossover between groups; the sample size has been adjusted accordingly.

Version Date: June 25, 2025 (v3.0)

Page **28** of **54**

[figure not shown]

**MAGICIAN** Clinical Trial Protocol

**9.14.**

**Follow up loss**

Due to the short follow-up period, we expect the loss to follow-up to be zero. In MAGNUM with the same follow-up interval, follow-up loss was 1/818. Studies of asthma and bronchiolitis from SickKids had follow up rates at 28 days approaching 100%.75,76 Conservatively, we anticipate the rate of the loss to follow up at 1%, although it will likely be lower.

**10. Adverse Events and Serious Adverse Events**

A Data Safety Monitoring Committee (DSMC) will be created to review this study, detailed in Section 11.2 (Safety Oversight – Data Safety and Monitoring Committee (DSMC)).

**10.1.**

**Definition of Adverse Events (AE)**

An Adverse Event (AE) is any untoward medical occurrence associated with the use of an intervention in a study participant, which does not necessarily have a causal relationship with the intervention. An AE can therefore be any unfavourable and unintended sign (including an abnormal laboratory finding), symptom or disease temporally associated with the use of the intervention, whether or not considered related to the investigational intervention. Stable chronic conditions which are present prior to entry in the study and do not worsen are not considered AE. These pre-existing conditions will be documented in the participant’s medical history.

A qualified physician, who is part of the study team, will be responsible for determining whether an AE is expected or unexpected, and the relationship to the study intervention will be described as unrelated, unlikely to be related, possibly related, probably related, or related, based on the temporal relationship to the administration of the study intervention and the study physician's clinical judgment.

An AE will be considered unexpected if the nature, severity, or frequency of the event is not consistent with the risk information previously described in section

2.3 (Risk/Benefit Assessment - Participant Safety) and Product Monograph for magnesium.

Adverse events will be collected using Common Terminology Criteria for Adverse Events (CTCAE) version 5.0.

**10.2.**

**Definition of Serious Adverse Events (SAE)**

Version Date: June 25, 2025 (v3.0)

Page **29** of **54**

[figure not shown]

**MAGICIAN** Clinical Trial Protocol

A Serious Adverse Event is any AE that is:

- fatal

•

•

•

•

•

life-threatening

requires or prolongs inpatient hospital stay

results in persistent or significant disability or incapacity a congenital anomaly or birth defect

an important medical event

The term “life-threatening” in the definition of “serious” refers to an AE in which the participant was at risk of death at the time of the event. It does not refer to an AE that hypothetically might have caused death if it were more severe.

Important medical events are those that may not be immediately life threatening but are clearly of major clinical significance. They may jeopardize the participant and may require intervention to prevent one of the other serious outcomes noted above. Examples of such medical events include allergic bronchospasm requiring intensive treatment in an emergency room or at home, blood dyscrasias or convulsions that do not result in inpatient hospitalization, or the development of drug dependency or drug abuse

**Serious Adverse Event (SAE)** will be documented for any incident that consist of:

1. hypotension below the 5th percentile for age requiring medical intervention within 180 minutes of the start of the experimental therapy, or
2. admission to intensive care unit (ICU) at the index ED visit.
3. admission to intensive care unit (ICU) for asthma within 72 hours after being discharged from ED.

These will be reported to the PI, SickKids REB, local REB and the DSMC.

Since hypotension is the only side-effect of IVMg occurring with appreciable frequency, all enrolled patients will be on precautionary frequent blood pressure monitoring as per the study protocol. If the systolic blood pressure drops below 5th percentile for age, treatment will be given as necessary and DSMC will be notified.

**10.3.**

**Classification of an Adverse Event**

**10.3.1. Severity of Event**

The following guidelines will be used to describe severity – as adapted from Common Terminology Criteria for Adverse Events (CTCAE) v5.0.

•

**Grade 1 Mild:** Mild; asymptomatic or mild symptoms; clinical or diagnostic observations only; intervention not indicated.

•

**Grade 2 Moderate:** Moderate; minimal, local or non-invasive

Version Date: June 25, 2025 (v3.0)

Page **30** of **54**

[figure not shown]

**MAGICIAN** Clinical Trial Protocol

intervention indicated; limiting age-appropriate instrumental activities of daily living (ADL), such as preparing meals, shopping for groceries or clothes, using the telephone, managing money.

•

**Grade 3 Severe:** Severe or medically significant but not immediately life- threatening; hospitalization or prolongation of hospitalization indicated; disabling; limiting self-care ADL, such as bathing, dressing and undressing, feeding self, using the toilet, taking medications, and not bedridden.

•

**Grade 4 Life-threatening:** Life-threatening consequences; urgent intervention indicated.

•

**Grade 5 Death:** Related to AE.

**10.3.2. Relationship to Study Intervention**

All Adverse Events (AEs) must have their relationship to the study intervention assessed by a qualified physician who is part of the study team based on temporal relationship and their clinical judgment. The degree of certainty about causality will be graded using the categories below.

•

**Definitely Related**– There is clear evidence to suggest a causal relationship, and other possible contributing factors can be ruled out. The clinical event, including an abnormal laboratory test result, occurs in a plausible time relationship to study intervention administration and cannot be explained by concurrent disease or other drugs or chemicals. The response to withdrawal of the study intervention should be clinically plausible.

•

**Probably Related** – There is evidence to suggest a causal relationship, and the influence of other factors is unlikely. The clinical event, including an abnormal laboratory test result, occurs within a reasonable time after administration of the study intervention, is unlikely to be attributed to concurrent disease or other drugs or chemicals, and follows a clinically reasonable response on withdrawal.

•

**Possibly Related** – There is some evidence to suggest a causal relationship (e.g., the event occurred within a reasonable time after administration of the study intervention). However, other factors may have contributed to the event (e.g., the participant’s clinical condition, other concomitant events).

•

**Unlikely to be related** – A clinical event, including an abnormal laboratory test result, whose temporal relationship to study intervention administration makes a causal relationship improbable (e.g., the event did not occur within a reasonable time after administration of the study intervention) and in which other drugs or chemicals or underlying disease provides plausible

Version Date: June 25, 2025 (v3.0)

Page **31** of **54**

[figure not shown]

**MAGICIAN** Clinical Trial Protocol

explanations (e.g., the participant’s clinical condition, other concomitant

treatments).

•

**Unrelated** – The AE is completely independent of study intervention administration, and/or evidence exists that the event is definitely related to another etiology.

